# Perceived dyspnea and experience of hospitalized patients with acute decompensated heart failure undergoing an early MObilization protocol with immersive Virtual rEality: MOVE study protocol for a parallel superiority randomized clinical trial

**DOI:** 10.1186/s13063-023-07786-z

**Published:** 2023-11-24

**Keywords:** Randomized clinical trial, Heart failure, Early mobilization, Cardiac rehabilitation, Virtual reality, Exercise tolerance, Patient experience

## Abstract

**Background:**

Immersive virtual reality (VR) is an innovative strategy for inpatient rehabilitation programs. Using immersive VR in early mobilization protocols has not yet been investigated in the setting of hospitalized patients with acute decompensated heart failure (ADHF), especially to improve perceived dyspnea, a common symptom of heart failure (HF).

**Methods:**

This is a single-center parallel superiority randomized clinical trial. The study will be conducted at a public teaching hospital in Brazil from January 2023 to January 2024. The sample will include adult patients with ADHF hospitalized for at least 24 h, randomly assigned in a 1:1 ratio to the control (standard early mobilization protocol conducted in the intensive care unit (ICU)) or intervention group (the same standard early mobilization protocol but associated with immersive VR). The primary outcome will be assessing perceived dyspnea, and the secondary outcome will be assessing patient experience.

**Discussion:**

Using immersive VR in early mobilization protocols in the ICU is expected to improve perceived dyspnea in patients with ADHF as well as patient experience regarding care. This study has the potential to increase patient adherence to early mobilization protocols in the setting of ADHF as well as to promote a positive patient experience. Filling this gap could promote the rational incorporation of technologies in health care.

**Trial registration:**

This study protocol is in its first version. ClinicalTrials.gov NCT05596292. Registered on 1 December 2022.

**Supplementary Information:**

The online version contains supplementary material available at 10.1186/s13063-023-07786-z.

## Introduction

HF is a highly prevalent clinical syndrome in which patients experience frequent episodes of decompensation that lead to periods of clinical instability and the need for admission to an ICU [1]. Repeated hospitalizations contribute to functional and cardiac decline [2, 3], and these deleterious effects are closely linked with previous conditions, especially in patients with a chronic disease that is difficult to manage [4].

Treatment in a critical setting often involves prolonged bed rest, imposing a series of limitations on daily activities. The prolonged use of pharmacological agents, diet changes, worsening of the disease, and physical inactivity further impair patients’ health, favoring the worsening of quality of life (QoL) [5]. Conventional methods of early rehabilitation, such as progressive walking, calisthenics and cycle ergometer use, have demonstrated their capacity to mitigate these negative consequences [6]. However, their application might be limited by patient discomfort, fatigue, dyspnea, or other clinical conditions. Thus, in recent years, alternatively to traditional inpatient rehabilitation programs, more attractive methods have been investigated aiming to improve patient experience and increase patient engagement during exercise. Immersive VR has a prominent role among these new technologies [7]. It blocks unpleasant stimuli and distracts patients from exercise-related stress, helping them manage common negative symptoms such as fatigue and dyspnea during physical exercise [8] and providing a break from the hospital environment [9].

Dyspnea is one of the main limiting symptoms in patients with HF. It is essential that both the subjective perception of breathlessness and the underlying physiological disturbances be considered [10]. Interventions should be designed with an understanding of this complex interplay, aiming to provide relief by targeting both aspects. In patients with ADHF, dyspnea is not just a symptom but a significant impediment to their rehabilitation and overall well-being. Traditional interventions, while beneficial [6], may not always offer immediate or substantial relief from the intense discomfort of dyspnea. This is where immersive virtual environments offered by VR come into play. VR can potentially redirect the patient’s focus from their discomfort, immersing them in a distraction that traditional methods might not provide [9]. By doing so, VR can alleviate the immediate sensation of breathlessness and provide a therapeutic avenue that complements traditional approaches.

In critical care settings, where dyspnea can delay or even interrupt inpatient rehabilitation, the rapid relief offered by VR might make it a superior option. Thus, while both traditional and VR interventions have their merits, the immersive and immediate nature of VR gives it a distinctive edge in addressing the challenges posed by dyspnea in patients with ADHF. However, despite VR studies with other populations [7, 9], studies in patients with HF are still scarce.

To date, no studies with a robust evidence level have investigated the safety of early mobilization in patients with ADHF admitted to ICU-level care. Therefore, further research should assess the feasibility and safety of early interventions, which may promote a more effective recovery and reduce hospitalization-related risks, as is already better established in the literature in other populations [11, 12]. Also, the distraction of VR can lead to reduced perception of dyspnea, which, in turn, can help provide a better experience during hospitalization. To the best of our knowledge, no published study assesses the improvement of parameters such as perceived dyspnea in patients with ADHF undergoing an immersive VR-assisted early mobilization protocol, nor aims to understand patient experience with this technology.

Filling this gap could improve the rational and direct incorporation of new technologies in health care, allowing for better outcomes in this clinically vulnerable population. This randomized clinical trial hypothesis is that patients hospitalized due to ADHF undergoing an early mobilization protocol with immersive VR will have improved perceived dyspnea as well as a positive patient experience with the technology compared with those undergoing a conventional mobilization protocol without immersive VR.

## Methods

### Study setting

This is a single-center parallel superiority randomized clinical trial blinded for primary outcome collection and data analysis. The study will be conducted at the Hospital de Clínicas de Porto Alegre (HCPA), a public teaching hospital in Brazil, from January 2023 to January 2024. This study protocol is in its first version and was registered at ClinicalTrials.gov under identification number NCT05596292 and is in accordance with the Standard Protocol Items: Recommendations for Interventional Trials (SPIRIT) [13] (Fig. 1). The SPIRIT Checklist for Trials is in the Additional file 2.

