### Intervention and groups

*CG:* participants in the CG will undergo a maximum of three standard early mobilization sessions in the ICU, with different exercise phases, as shown in Table 1.

**Table 1 Tab1:** Early mobilization protocol phases

Stage	Intervention
Day 1	In-bed cycle ergometry in sitting position, 5 min for upper limbs and 5 min for lower limbs
Day 2	Day 1 + training in orthostatic position
Day 3	Walking for 5 to 10 min

Source: Early mobilization protocol adapted from Delgado et al. [6]

*IG:* participants in the IG will undergo a maximum of three standard early mobilization sessions in association with the use of an immersive VR headset (VR Shinecon G10), with different exercise phases, as previously described. Immersive VR headsets are compatible with smartphones (Samsung A30), allowing patients to interact with a 360-degree YouTube video (https://youtu.be/h_0oimKWlNs) while listening to lo-fi music on Spotify (https://open.spotify.com/track/7qcWkecFox8uO6mYyYwpy6?si=qDYj9_kpSCiPsXNRirFrYQ) through wireless earbuds (Multilaser Joy PH308 Bluetooth sports headphone with microphone).

Tolerance will be considered and assessed using the Borg scale, vital signs, and the patient’s response to the following question: “In your opinion, were you able to tolerate this exercise well?” (yes or no).

Participants who can tolerate the exercise at a given stage may move on to the next stage in the same session. The participant will repeat the same exercise from the previous stage before performing the next exercise. If the patient fails to complete one of the phases, the intervention can be interrupted to respect the patient’s tolerance. Likewise, if the patient initiates but fails to complete the protocol on the second day, a new attempt will be made on the third day, beginning on the stage the patient was previously on.

In addressing the rationale for the intervention dosage in both groups, it is paramount to understand the patients’ profiles. Patients with ADHF often experience significant dyspnea at rest and demonstrate low exercise tolerance. By the time the early mobilization protocol is initiated, after 24 h of hospitalization and with the approval of the medical team, patients have usually achieved a level of stability. However, they are still likely to have symptoms that restrict their participation in conventional exercise programs.

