### Blinding

Patient randomization will be conducted by a researcher not involved in data collection. Physical therapists will be blinded for the collection of the outcomes (perceived dyspnea and patient experience) and data analysis. Data will be collected by researchers uninvolved in the intervention but who are not blinded to group allocation due to the nature of the protocol and the outcomes. Data analysis will be performed by a statistician independent from the study.

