
### Data collection

The primary outcome should be assessed immediately before and after each mobilization therapy session, less than 5 min before the start and immediately after the completion of the mobilization protocol.

At the end of the interventions, patient experience will be assessed in both groups. Patients included in the study will be contacted in the ICU within 48 h of the end of the intervention and will be invited to answer questions related to their experience during the mobilization protocol with and without the use of immersive VR.

The outcomes will be collected by two researchers previously trained in the pilot study. The researchers involved in data collection are not involved in applying the study protocol and are not blinded to group allocation due to the nature of the protocol and the outcomes assessed, such as patient experience.

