### Potential biases

Participants will not be blinded to their allocation group. The researchers responsible for the intervention in both groups will not be involved in collecting primary and secondary outcomes. The researchers responsible will not be blinded to collecting outcomes due to the relationship between the use of immersive VR, clinical results, and patient experience.

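### The trial is described as blinded for collection of the primary outcome, yet neither the patient who rates dyspnea nor the researcher who asks for the rating is blinded

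*Protocol article*

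**What the plan says.** Study setting gives the design in one line: a "single-center parallel superiority randomized clinical trial blinded for primary outcome collection and data analysis". Four other parts of the Methods bear on this.

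- **Blinding.** On the therapists: "Physical therapists will be blinded for the collection of the outcomes (perceived dyspnea and patient experience) and data analysis". On those who gather the data: "Data will be collected by researchers uninvolved in the intervention but who are not blinded to group allocation". The analysis is assigned to a statistician independent of the study.
- **Data collection.** Two trained researchers collect the outcomes. They "are not involved in applying the study protocol and are not blinded to group allocation due to the nature of the protocol".
- **Potential biases.** Participants are not blinded to their group. Those who deliver the sessions take no part in collecting the primary and secondary outcomes. The section adds: "The researchers responsible will not be blinded to collecting outcomes".
- **Study variables.** Dyspnea is the patient's rating from 0 to 10 on the illustrated modified Borg scale, at rest and immediately after each session. One of the data-collecting researchers asks for it.

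Intervention and groups also uses the scale for a second purpose: "Tolerance will be considered and assessed using the Borg scale, vital signs". A yes-or-no question to the patient is the third element of that assessment.

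**The concern.** A reader who meets blinded collection of the primary outcome in a design statement takes it to mean that whoever obtains the outcome does not know the treatment group. Here the outcome is a perceived symptom. The intervention is a headset with video and music, which cannot be concealed from the patient, and the hypothesis is that this distraction lowers perceived dyspnea. In such a setting, blinding of outcome collection is one of the first things a reader looks for when judging whether a difference in ratings reflects the treatment or the expectations of patient and interviewer.

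If the design statement is wrong on this, anyone who relies on it, including someone rating risk of bias for a systematic review, will credit the trial with protection that it lacks. A positive dyspnea result would then be read as stronger evidence than the design can give.

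**Working it through.** No formula applies and the plan gives no figure to reproduce, so the check is a comparison of statements. Blinding of a rating requires that at least one person who shapes it does not know the allocation. The steps take each person in turn.

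1. **The patient, who gives the rating.** Potential biases says that participants are not blinded. Result: unblinded.
2. **The researcher who asks for the rating.** Study variables assigns this to one of the data-collecting researchers. Blinding and Data collection each say outright that these researchers are not blinded to allocation. Potential biases agrees in looser words, since it literally speaks of not being blinded to the collecting of outcomes. Result: unblinded, with two explicit statements and one looser one.
3. **The therapists.** Blinding says that they are blinded for the collection of outcomes and the analysis. It does not say that they are blinded to allocation, and they could hardly be, because the headset is used during the session. By the article's own account they do not collect the outcome, so their position cannot make its collection blinded.
4. **The statistician.** Study setting claims blinded analysis and Blinding adds independence. The two are compatible. Independence is not the same as working without knowledge of group, but no section says that the analyst will know the groups. Result: not contradicted.

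For collection of the primary outcome, steps 1 and 2 leave nobody masked. The design statement is therefore wrong in its first half and uncontradicted in its second.

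**When the rating is taken.** Data collection places it less than 5 minutes before and immediately after each session. Participant timeline places these session assessments after randomization. Expectation or interviewer influence can thus act on the endpoint itself.

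**Use of the Borg scale for tolerance.** Intervention and groups uses the scale to assess tolerance, and a patient who tolerates a stage may go on to the next in the same session. The sentence names no one who takes or sees the score. Participant timeline speaks of a team that both conducts the intervention and collects variables, which blurs the separation of roles described elsewhere. The article leaves it unclear how therapists are kept apart from dyspnea scores during a session.

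**The case against.** The strongest reply is that nothing is concealed. The lack of blinding of patients and collectors is disclosed in a section headed Potential biases, and for collectors it is repeated, with reasons, in two others. Open-label collection of a self-reported symptom is a natural consequence of a headset intervention. On this view one phrase in Study setting is wrong and the trial itself is no worse for it. That is fair as to the design: the fault is an inconsistency, and the article does not hide the risk of bias. It does not rescue the phrase, because both versions are in print and only one can be true.

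A second reply is that the phrase refers to the therapists. Their sentence in Blinding fits with Potential biases as a separation of roles: those who treat do not collect outcomes. That is a real safeguard and should stay in the text. It is not masking of the assessor to allocation, which is what the phrase conveys.

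Three stronger readings are tempting and should be resisted.

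- A reader might infer that the therapists use the Borg score and so cannot be blinded to dyspnea. No section says so. The tolerance sentence is passive, and a collector could take the score. The gap justifies a clarification and no more.
- A reader might infer that the whole blinding statement is false, including the analysis. An independent statistician is consistent with blinded analysis, and how groups are coded in an export is commonly left to a fuller document that is not shown here.
- A reader might want to put a number on the bias. The article gives no basis for one.

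**Conclusion.** The point holds, limited to collection of the primary outcome. The article claims blinding there, and its own account shows that neither the patient nor the collector is blinded. This should be corrected because it misdescribes a basic property of the design for a subjective primary outcome.

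Its size cannot be estimated from the document. Expectation or interviewer influence could add to the between-group difference, and the only reference is the 1 Borg point that the Sample size section treats as relevant. The article supports no particular amount of bias and does not show that bias will occur. The conclusion rests only on the plain meaning of the quoted statements and on reading blinded outcome collection in its usual sense, as ignorance of allocation by those who obtain the outcome. The therapists' sentence and the claim of blinded analysis need clearer wording, but neither is shown to be false.

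**What to change.** 1. **Study setting:** remove the claim that primary outcome collection is blinded. State that participants and outcome collectors know the allocation.
2. **Potential biases, and later the results report:** say that a positive dyspnea finding is open to expectation and interviewer bias and is to be interpreted accordingly. Reword the sentence on the researchers so that it says plainly that they know the allocation.
3. **Blinding:** replace the therapist sentence with a statement that those who deliver the sessions do not collect outcomes, described as separation of roles and not as masking to allocation.
4. **Intervention and groups:** say who takes the Borg score used for tolerance, and reconcile this with the reworded Blinding section and with the mention of a single team in Participant timeline.
5. **Data analysis:** keep the claim of blinded analysis and support it by giving the independent statistician a dataset with coded groups. Data management says that data are extracted only once the full number of participants has been included, so this can still be arranged.

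The cost is a less favourable description of blinding and one coded export. Changing who collects the rating, for instance by hiding the headset from one collector, is not recommended. It would leave the patient unblinded. It would also change how the primary outcome is collected late in recruitment, which began in January 2023 and was due to end about January 2024, with the article published in November 2023.

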**Fig. 1 Fig1:**
[figure not shown]
Timetable for inclusions, interventions, and assessments. ^1^Risk of falls accessed by Severo-Almeida-Kuchenbecker 2 score and functional independence accessed by Barthel scale. ^2^Age, sex, education, current and previous hospitalization, disease condition, associated comorbidities, and medication use. ^3^Borg Rating of Perceived Exertion Scale. ^4^Net Promoter Score, Likert scale, and interview

The Research Ethics Committee of the HCPA and the Universidade Federal do Rio Grande do Sul (UFRGS) approved this study before data collection, under registration number 62209822.7.0000.5327. The research team will be responsible for the integrity of this study.

### Participants

Patients admitted to the hospital’s ICU with a medical diagnosis of ADHF will be included in the study. The medical diagnosis will be made by the hospital team at ICU admission, based on anamnesis, symptomatology, and necessary complementary tests (ejection fraction verified by echocardiography). The research team is not involved in the diagnosis.

Participants will be randomly assigned to two groups, as shown in Fig. 2:Control group (CG): participants will undergo three sessions of conventional treatment consisting of an inpatient early mobilization protocol conducted in the ICU.Intervention group (IG): participants will undergo three sessions of conventional treatment consisting of an inpatient early mobilization protocol conducted in the ICU with the use of an immersive VR headset.

**Fig. 2 Fig2:**
[figure not shown]
Description of the study protocol. Source: Research team

### Eligibility criteria

#### Inclusion criteria

18 years or older.Diagnosis of ADHF in the medical records.Be lucid and coherent.Be hospitalized for at least 24 h.Have the authorization of the medical team for inclusion.Patients with intermittent noninvasive ventilation can be included in the study and undergo the early mobilization protocol in the intervals of this therapy.

#### Exclusion criteria

Patients with invasive mechanical ventilation or circulatory support (extracorporeal membrane oxygenation).Patients with neurodegenerative diseases.Pregnant patients.Patients with hemodynamic instability (characterized by symptomatic hypotension with systolic blood pressure equal to or less than 80 mmHg and diastolic blood pressure equal to or less than 50 mmHg, heart rate above 130 bpm or below 40 bpm at rest, oxygen saturation below 90% with spontaneous ventilation or oxygen support).Patients with modified Borg scale score ≥ 4 at rest.Patients with difficulty communicating.Patients who cannot adapt to wearing an immersive VR headset.

### Intervention and groups

*CG:* participants in the CG will undergo a maximum of three standard early mobilization sessions in the ICU, with different exercise phases, as shown in Table 1.

**Table 1 Tab1:** Early mobilization protocol phases

Stage	Intervention
Day 1	In-bed cycle ergometry in sitting position, 5 min for upper limbs and 5 min for lower limbs
Day 2	Day 1 + training in orthostatic position
Day 3	Walking for 5 to 10 min

Source: Early mobilization protocol adapted from Delgado et al. [6]

*IG:* participants in the IG will undergo a maximum of three standard early mobilization sessions in association with the use of an immersive VR headset (VR Shinecon G10), with different exercise phases, as previously described. Immersive VR headsets are compatible with smartphones (Samsung A30), allowing patients to interact with a 360-degree YouTube video (https://youtu.be/h_0oimKWlNs) while listening to lo-fi music on Spotify (https://open.spotify.com/track/7qcWkecFox8uO6mYyYwpy6?si=qDYj9_kpSCiPsXNRirFrYQ) through wireless earbuds (Multilaser Joy PH308 Bluetooth sports headphone with microphone).

Tolerance will be considered and assessed using the Borg scale, vital signs, and the patient’s response to the following question: “In your opinion, were you able to tolerate this exercise well?” (yes or no).

Participants who can tolerate the exercise at a given stage may move on to the next stage in the same session. The participant will repeat the same exercise from the previous stage before performing the next exercise. If the patient fails to complete one of the phases, the intervention can be interrupted to respect the patient’s tolerance. Likewise, if the patient initiates but fails to complete the protocol on the second day, a new attempt will be made on the third day, beginning on the stage the patient was previously on.

In addressing the rationale for the intervention dosage in both groups, it is paramount to understand the patients’ profiles. Patients with ADHF often experience significant dyspnea at rest and demonstrate low exercise tolerance. By the time the early mobilization protocol is initiated, after 24 h of hospitalization and with the approval of the medical team, patients have usually achieved a level of stability. However, they are still likely to have symptoms that restrict their participation in conventional exercise programs.

All participants will have individual rooms, and the ambulation stage of both groups will be performed in a parallel corridor, where seeing the other patients hospitalized in the unit is impossible, ensuring their privacy.

